# The effect of a probiotic on gastrointestinal symptoms due to menstruation in healthy adult women on oral contraceptives: randomized, double-blind, placebo-controlled trial protocol

**DOI:** 10.1186/s13063-022-06410-w

**Published:** 2022-06-10

**Keywords:** Women’s health, Gastrointestinal, Menstruation, Microbiome, Probiotic, *Bifidobacterium*

## Abstract

**Introduction:**

For many women, uncomfortable and stressful symptoms accompany the menstrual cycle each month, sometimes in a debilitating manner. Previous studies have reported that gastrointestinal symptoms in healthy women significantly differ by the day of the menstrual cycle, but few studies have assessed interventions intended to minimize these symptoms. Probiotics supplements have been shown to attenuate gastrointestinal symptom severity as well as self-reported feelings of stress in various populations. This study evaluates the effect of a probiotic on abdominal pain and gastrointestinal symptoms in healthy women who take an oral contraceptive, have regular menses, and typically experience these symptoms during menstruation with the primary aim being change in abdominal pain intensity related to the menstrual cycle with probiotic versus placebo supplementation.

**Methods and analysis:**

In this randomized, double-blind, placebo-controlled parallel study, participants will receive either a probiotic or placebo supplement. Participants will begin answering questionnaires approximately 7 days before the start of menstruation (i.e., active bleeding), and 3 days later, they will begin consuming the study supplement for 8 weeks. The questionnaires administered will collect data about abdominal pain severity (primary outcome) and duration related to the menstrual cycle, digestive health, dietary intake, stress, and digestion-associated quality-of-life. A subgroup of women will provide weekly vaginal swabs and stool samples to examine the effect of the probiotic supplement on microbiota composition and diversity for exploratory purposes. Two-sided tests using a linear model and a type I error rate of *α* = 0.05 will be employed to test all hypotheses. Continuous variables will be presented as means with standard errors and categorical variables, as counts or proportions.

**Ethics and dissemination:**

This study was reviewed and approved by the University of Florida Institutional Review Board 01. Written informed consent will be obtained from all participants prior to any study activities. Study findings will be disseminated at scientific conferences and publication in the trial registry or in a peer-reviewed journal. Any protocol amendments will be reported in the final manuscript of this study.

**Trial registration:**

ClinicalTrials.gov NCT04457401. Registered prospectively on 07 July 2020. The trial was completed in December of 2021.

**Protocol version:**

V4.0 (11-04-2020)

**Trial status:**

Currently recruiting. Recruitment began in November 2020 and extend until December 2021.

## Strengths and limitations

This study is novel in that healthy women will be prospectively followed daily for an 8-week intervention period and will not be subject to recall bias.This study will be conducted in healthy individuals, defined as women who do not have a physician diagnosed gastrointestinal or gynecological disease. Previous studies have focused on women with various diseases or conditions such as endometriosis or irritable bowel syndrome, for example.A probiotic will be used to help mitigate gastrointestinal symptoms during the menstrual cycle.This study will recruit throughout the contiguous United States to ensure a more heterogeneous population.This study is limited in that only women who consume oral contraceptives qualify to participate. This may limit the generalizability of the present study to women who actively take combination oral contraceptives.The findings of this study may only have implications in women who do not have gastrointestinal and gynecological diseases. Future studies, however, may be conducted in other populations of women to present more broad findings.

## Introduction

Menstruation is a period of time that brings discomfort for many women. Women with various gastrointestinal or gynecological diseases or conditions may experience negative side effects from the menstrual cycle due to their diagnosis; however, many healthy women without these diseases or conditions may also experience uncomfortable symptoms. Healthy menstruating females experience several physiological symptoms on the first few days of menstruation such as abdominal pain, headaches, bloating, diarrhea, and constipation [1, 2] and have increased psychological concerns such as stress and anxiety [3]. While these symptoms are commonly recognized to affect a large portion of the female population, few interventions have been studied to assist in managing this discomfort. Some clinicians may direct their patients to take pain relieving medications without any thoughts on the consequences of chronic use [4]. When specifically consuming nonsteroidal anti-inflammatory drugs for menstrual related pain, the risk of adverse events such as nausea and indigestion is significantly increased compared to placebo consumption [5]. According to a recent study that prospectively characterized gastrointestinal (GI) symptoms throughout the menstrual cycle in women taking oral contraceptives, syndrome scores for abdominal pain, diarrhea, constipation, and indigestion (as measured by a modified daily version of the Gastrointestinal Symptom Rating Scale [6]) were all significantly different on the first day of menstruation than many other days during the menstrual cycle [7].

In addition to increased GI symptoms, self-reported stress also significantly increased on day 1 of menstruation and remained relatively high for the first few days of menstruation [7]. Stress has been correlated with GI symptoms through the gut-brain axis pathway [8]. Increased stress in the first days of menstruation is perhaps impacting GI function, and, in turn, GI symptoms related to menstruation may be contributing to overall stress. Severe abdominal cramping, such as dysmenorrhea, has also been associated with increased stress [9]. Dysmenorrhea is characterized as painful uterine spasms or severe abdominal cramps during menstruation [10]. Regardless of the order of occurrence, increased abdominal pain and stress on day 1 of menstruation may contribute to the observed increase in overall GI symptoms, increased stool frequency, and softer stool consistency observed in these women who were taking oral contraceptives (OC) [7].

Prostaglandins seem to be the major players in the induction of menstrual pain. Prostaglandin production and release still occurs in women on OC but to a lesser extent [11]. The GI tract may also respond to prostaglandin release during menstruation, which may explain changes in stool form and abdominal pain [12]. Prostaglandins may either increase or decrease intestinal motility, decrease gastric acid secretion, and modulate hepatic glycogen and glucose metabolism [12, 13]. The effects of prostaglandins may directly or indirectly contribute to the GI and emotional stress that is associated with menstruation. Regardless of the exact cause of GI symptoms and emotional stress, there is a need for an intervention that can help maintain physiological and psychological health throughout the menstrual cycle.

A proposed intervention to normalize GI function across the menstrual cycle is to supplement the diet with probiotics. Various probiotic supplements have been shown to effectively decrease diarrhea, constipation, stress, and intestinal permeability, as well as impact immunologic outcomes [14–16]. Probiotics also modulate stool form, as measured by the Bristol Stool Form Scale, to provide a more favorable consistency [17]. In particular, endogenous *Bifidobacterium* spp. vary throughout life in healthy humans and in disease states and have been associated with various beneficial health effects [18, 19]. Notably, *Bifidobacterium* strains are effective in decreasing stress, abdominal pain, and other gastrointestinal symptoms [14, 20–28]. Menstruation is generally associated with these types of symptoms [29–32], and specifically, stool form and self-reported stress are significantly different on the first day of menstruation compared with many other days throughout the menstrual cycle of healthy women on combination oral contraceptives [7]. Investigating the effects of a probiotic supplement in otherwise healthy women experiencing GI symptoms and stress during menstruation is warranted. Therefore, the primary aim of this study is to determine the effect of a probiotic on menstruation-related GI symptoms and self-reported stress throughout the menstrual cycle in healthy women on oral contraceptives.

### Objectives

The primary outcome of this clinical trial will assess the change in menstruation-related abdominal pain recorded over the first 3 days of menstruation while on the intervention compared with a similar time period during baseline between women on the probiotic versus placebo. Secondary outcomes will determine the effect of the probiotic on menstruation-related GI symptoms and function, self-reported stress, dietary intake, and food cravings. Exploratory analyses in a subgroup of participants will examine changes in the fecal and vaginal microbiome throughout the menstrual cycle.

## Methods and analysis

### Overall design

This 9-week randomized, double-blind, placebo-controlled clinical trial will be conducted online across the contiguous United States and at the University of Florida (i.e., exploratory subgroup providing biological samples), in accordance with the International Conference on Harmonizaiton-Good Clinical Practice (ICH-GCP) guidelines. This study observes a two-arm parallel design with a 1:1 allocation, including an exploratory subgroup providing fecal and vaginal swab samples. A diagram detailing the study flow is shown in Fig. 1. The protocol was prospectively registered on ClinicalTrials.gov; the database record (NCT04457401) will be updated to reflect any amendment to this protocol over the course of the study.

**Fig. 1 Fig1:**
[figure not shown]
Schematic of the study design and flo

### Recruitment

Recruitment started in November 2020 and will continue over a period of 6 months. Healthy females aged 18 to 35 years who are taking OC will be recruited for this study, as OCs are expected to reduce the likelihood of unpredictable or unscheduled bleeding and to provide a more homogeneous population in regard to hormonal variability. The age range was determined to exclude women who may experience premature menopause [33]. Potential participants will be recruited by distributing printed flyers and handouts, sending emails, word of mouth, and by posting on social media. Participation will be open to anyone who meets the inclusion and exclusion criteria and has internet access. After informed consent is obtained from a trained study coordinator online using RedCap [34] and methods approved by the University of Florida’s Institutional Review Board-01, participants will self-screen based on the following criteria:

#### Inclusion criteria

18–35 years of age (inclusive);Regularly menstruating (i.e., approximately every 24 to 33 days);Typically have an average of at least mild abdominal pain (score of 3 or above on the GSRS screener) during the first 3 days of menstruation;Currently using a combination OC;Willing to discontinue the use of any probiotics, including supplements and foods labeled with “probiotic,” for the 2 weeks preceding the study and throughout, and to discontinue the use of fiber supplements during the study;Typically have one stool per day (subgroup).

#### Exclusion criteria

Using a birth control implant, vaginal ring, shot, patch, or IUD;Lactating or known to be pregnant;Currently on treatment for a physician-diagnosed GI or gynecological disease or condition;Experiencing pain that is caused by a disorder of reproductive organs including endometriosis, adenomyosis, uterine fibroid, or a pelvic infection;Use of another investigational product within 3 months of screening;Antibiotics or probiotic supplements consumed within 1 month before screening;Allergy to milk, soy, or yeast.

Participants may withdraw from the study at any time. They are encouraged to contact a study coordinator to withdraw from the study. Some participants may discontinue study activities without notice, in which case they will be consider lost to follow up. The principal investigator may withdraw participants as well if they no longer meet the inclusion and exclusion criteria.

### Randomization, sequence concealment, and blinding

This is a double-blind study; the sponsor representatives involved in the study, the investigators, the participants, and any health care professional or site personnel involved in participant management or outcome assessment will remain blinded. Participants will be stratified on their typical abdominal pain score at the beginning of the study and randomized to either the probiotic or placebo supplement in blocks of a pre-specified size. This abdominal pain score will reflect the first 3 days of their typical menstrual cycle and will be on a scale of 3 (mild discomfort) to 7 (very severe discomfort). To maintain a balance in numbers of participants in the main and subgroup studies, randomization will be conducted separately for the main and subgroup studies. Participants will be stratified into two groups including those with mild abdominal pain (score of 3) and those with moderate to very severe abdominal pain (scores 4–7).

#### Sequence generation and allocation concealment:

The randomization sequence will be generated using a random-number generator and will be provided in opaque, sealed envelopes by an individual who will not have contact with the participants. Six unique four digit codes will be used for each supplement (6 different codes for the probiotic and six different codes for the placebo) in the event that an adverse reaction requires unblinding of one of the codes due to a participant reported adverse event. All supplement bottles will be identical and packaged the same way.

#### Implementation

After participants provide their informed consent and eligibility is confirmed, they will be assigned a study number based on the order that they consented. Participants will then be assigned to a week to begin the study based on when their next menstrual event occurs. Within each week, participants will be randomized by a co-investigator ([name]) based on the order that they consented. Only the study number will be used during the study to identify participants, and all data will be permanently anonymized after study completion.

### Study conduct

The schedule of activities is presented in Table 1. After providing informed consent for the main group and subgroup, participants will self-report their height, weight, and typical fiber intake using a fruit, vegetable, and fiber screener (NutritionQuest) [35]. Participants will complete a demographics questionnaire where they will be asked to estimate the approximate date of their next menstrual event to determine their allocation date. All study days will be ± 3 days to account for variation in each participant’s menstrual cycle.

**Table 1 Tab1:**
[figure not shown]
Schedule of activities

^a^Study days may vary due to variability in menstrual cycle length

^b^Each cycle and its assessments will be based on the first day of menstruation (first day of bleeding)

^c^Probiotic or Placebo

Following consent and approximately 1 week before menstruation, participants will be asked to complete a pregnancy test and will begin completing daily questionnaires. Briefly, daily questionnaires will inquire about GI symptoms, abdominal pain as measured by the visual analog scale [36–40], duration of abdominal pain, stress, stool form, stool frequency, adverse events, and medications taken, including the dose and administration schedule. Study days 3, 28, and 56 will be referred to as “menstruation 1,” “menstruation 2,” and “menstruation 3,” respectively. On the third day of their menstrual cycle (day 3/menstruation 1), they will begin consuming their study supplement (start of intervention). On the days participants experience GI symptoms related to the menstrual cycle, they will answer an additional questionnaire, which is a modified daily version of the GSRS to access GI symptoms. Approximately 7 days prior to menstruation 1 (study day − 7) and 3 days after each menstrual event (study days 3 and 31), participants will answer the Menstrual Symptom Questionnaire to assess symptoms leading up to and during menstruation. Seven days after each menstrual event (study days 7, 35, and 59), participants will be administered the Perceived Stress Scale to assess stress levels over the previous month [41]. Participants will also answer two validated weekly questionnaires including the GSRS and the Digestion-associated Quality of Life Questionnaire each week they are in the study. Each participant will also complete a 24-h dietary recall assessment at four points during the study (study days − 7, 21, 28, and 35) throughout the menstrual cycle. Finally, participants will also complete the Food Cravings Inventory (FCI) during the first and second menstrual event (study days 1 and 28). Participants will complete all questionnaires online using their assigned study number to maintain confidentiality. Questionnaires will be administered via Qualtrics Survey Software (Qualtrics Software Company) and data will be maintained on password-protected, encrypted computers.

While we will encourage participants to avoid pain relievers, consumption of over the counter pain relievers to assist with the pain associated with the menstrual cycle will be allowed for ethical reasons. We will ask participants to report any pain reliever consumption and instruct them to report their greatest abdominal pain intensity prior to consumption.

A subgroup of 20 participants per arm will also be asked to sign a separate informed consent form which will detail all of the main study tasks and will also include information on providing ten stool and vaginal swab samples during the study (study days − 7, 1, 7, 14, 21, 28, 35, 42, 49, and 56). These participants will be provided with stool and vaginal swab collection kits and receive instructions on how to self-collect these samples at home. Participants will be asked to return the samples to the study site. This subgroup will also complete additional 24-h dietary recalls (study days 1, 42, 49, and 56).

Participants will continue to answer daily questionnaires until the third day of their third menstrual cycle, at which point they will discontinue answering questionnaires and consuming the study supplement. At the conclusion of the study, blinding efficacy will be assessed via a questionnaire asking participants which supplement they thought they were consuming. Participants will be instructed to either return any unused capsules or text a picture of the remaining capsules to the study coordinator for compliance assessment.

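### The third Perceived Stress Scale day contradicts its own seven-day rule and the end of questionnaires, and no listed administration of the scale precedes the supplement

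*Protocol article*

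**What the plan says.** All the timing statements are in the protocol article under Study conduct, in the text around Table 1.

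- Stress scale: "Seven days after each menstrual event (study days 7, 35, and 59), participants will be administered the Perceived Stress Scale to assess stress levels". The recall period is given as the previous month.
- Menstruation days: "Study days 3, 28, and 56 will be referred to as “menstruation 1,” “menstruation 2,” and “menstruation 3,” respectively". A footnote to Table 1 ties each cycle's assessments to the first day of bleeding.
- Supplement start: "On the third day of their menstrual cycle (day 3/menstruation 1), they will begin consuming their study supplement".
- End of data collection: daily questionnaires continue "until the third day of their third menstrual cycle, at which point they will discontinue answering questionnaires and consuming the study supplement".
- Every study day carries a window of plus or minus 3 days.

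Under Study outcomes, stress is a secondary outcome measured in two ways: daily self-report and the monthly Perceived Stress Scale. Under Statistical analysis, the general test is on the mean change from before to after supplementation. The article does not name the day-7 score as the baseline for this scale, but it lists no earlier one.

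**The concern.** Two features of the calendar do not fit the rest of the plan.

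First, the rule and the day list disagree for the third assessment, and the day that the rule implies lies beyond the point at which participants stop answering questionnaires. Site staff programming the online survey could follow the rule, the list or the stopping point, and would not get the same date from each.

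Second, the first administration follows the start of the supplement. A change score needs a value from before treatment. Here the earliest available value already includes some days on product, so any rapid effect would sit partly in the value that is subtracted. What is at stake is the interpretability of one of the two measures of a secondary outcome.

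**Working it through.** **Inputs.** From Study conduct: scale on days 7, 35 and 59; menstruations labelled days 3, 28 and 56; first capsule on day 3; window of plus or minus 3 days; questionnaires end on day 3 of the third menstruation. Assumed: a recall month of 28 to 30 days, since the article gives no number of days.

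**1. Does the rule reproduce the listed days?** Rule: menstruation day + 7.

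- Second: 28 + 7 = 35. Reproduced.
- Third: 56 + 7 = 63. Listed as 59, which is 4 days short. Its actual offset is 59 − 56 = 3 days.
- First: this depends on how menstruation 1 is dated. From day 0, the offset is 7 − 0 = 7; from first bleeding on day 1, 7 − 1 = 6; from the label day 3, 7 − 3 = 4.

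The offsets are therefore 7, 7, 3 or 6, 7, 3 or 4, 7, 3. The third is 3 days on every reading. Day 59 does fit a three-day rule, like the one used for the Menstrual Symptom Questionnaire (28 + 3 = 31; 56 + 3 = 59).

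**2. Can day 63 be collected?** Day 3 of a menstruation starting on day 56 is day 58, or day 59 if counted as 56 + 3. Day 63 is 4 to 5 days later. Even the early edge of its window, 63 − 3 = 60, falls after questionnaires have stopped on that nominal calendar.

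**3. How much of the first recall month is on product?** From day 3 to day 7 there are 7 − 3 = 4 elapsed days, or 5 counting both ends.

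- 4/30 = 13%; 4/28 = 14%; 5/30 = 17%; 5/28 = 18%.
- With the first scale anywhere from day 4 to day 10 (the window) and elapsed days counted: 1/30 = 3% up to 7/28 = 25%.

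**4. What does that do to the change score?** Let E be the between-arm effect in the later score and s the fraction of E already in the first score. The between-arm difference in change is E − sE = E(1 − s).

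- Immediate full effect, equal weighting of recalled days: s equals the share in step 3, so 13 to 18% at the nominal day.
- Effect growing linearly from 1 unit on day 3, 30-day recall: the first score carries (1 + 2 + 3 + 4 + 5)/30 = 0.5 units. The day-35 score (days 6 to 35) averages (4 + 33)/2 = 18.5, and the day-59 score (days 30 to 59) averages (28 + 57)/2 = 42.5. Then s = 0.5/18.5 = 2.7% or 0.5/42.5 = 1.2%.
- No effect in the first days: s = 0.

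**5. What period does each score cover?** With a 28-day recall the windows are days −20 to 7, 8 to 35 and 32 to 59. Each holds the first 3 days of exactly one menstruation (days 1–3, 28–30 and 56–58). With a 30-day recall the last window also takes in day 30. The last two windows overlap by 4 days (28-day recall) or 6 days (30-day recall), all of them on product.

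**The case against.** The best defence is that day 59 matches the end of questionnaires and may be a deliberate final assessment under a loosely worded rule. Table 1, which holds the schedule itself, is not available here. That explanation is plausible, but the running text still states a rule and a list that disagree, so the reconciliation is needed either way.

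A reader might infer more than the documents support, in four ways:

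- *That the uneven offset mixes cycle phases and makes the third score incomparable.* The Introduction reports that stress stays relatively high over the first days of bleeding, but that concerns daily ratings. A month-long recall covers about one cycle each time; what changes is mainly how recent the menses are at completion.
- *That the uneven offset pulls the treatment difference toward zero.* It is common to both randomised arms, so by itself it can add noise or a common shift and no more.
- *That stress has no baseline at all, or no other measure.* Daily self-reported stress starts about a week before menstruation 1 and so precedes the supplement. The article does not describe the Perceived Stress Scale as its only validated stress measure.
- *That the on-product share is far larger.* The abstract's timing of the supplement can be read as a start on day −4, giving 11/30 to 11/28, or 37 to 39%. Study conduct and Study outcomes both support a start on day 3.

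It is also fair to say that the sentence on change scores is general and the contrast for this scale is not spelled out. A comparison of later scores alone would not carry the attenuation.

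**Conclusion.** The point holds in two limited parts. The seven-day rule, the listed day 59 and the end of questionnaires cannot all stand: the third assessment is 4 days short of the rule however menstruation 1 is dated, and the rule's own day cannot be collected as planned. Separately, no listed Perceived Stress Scale score is fully pre-supplement.

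The second part could attenuate the between-arm change on this scale by up to about 13 to 18% at the nominal day. That bound assumes a 28- to 30-day recall, a full effect from the first capsule and equal weighting of recalled days; it could be higher if recall favours recent days. Under gradual onset it is about 1 to 3%, and under delayed onset zero. The figure should not be quoted as an expected bias.

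The effect is confined to one measure of one secondary outcome. The primary outcome uses pain scores from before the supplement starts and, like the sample size, is unaffected.

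**What to change.** Reconcile the rule, the day list and the end of questionnaires in a single schedule statement that meets two conditions:

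- the first scale is completed before the first capsule, for example at day −7 or on day 3 before intake;
- one stated offset from first bleeding is used in all cycles, falling no later than the last questionnaire day.

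Day 3 of each menstruation, with the first scale completed before intake, meets both. Day −7 gives a clean baseline but meets the second condition only if the later assessments move as well. The Menstrual Symptom Questionnaire is listed for days −7, 3 and 31 only, so the third stress scale would not coincide with it.

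The cost is one line in the schedule and a changed survey trigger date, with no added instrument or visit. The article's trial registration entry reports completion in December 2021. If the data are already collected, report the actual day of the third assessment, state that the day-7 score is not a pure baseline, and read this scale alongside daily stress.

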The secondary outcomes are defined as follows:To determine the effect of the probiotic on the number of days with abdominal pain (score above 0), assessed by the daily visual analog scale. We hypothesize that women who consume the probiotic will experience a decrease in the number of days with abdominal pain.To determine the effect of the probiotic on GI symptoms throughout the menstrual cycle, as measured by a daily modified version of the GSRS. We hypothesize that women who consume the probiotic will experience a decrease in the severity of GI symptoms compared to women who consume a placebo.To determine the effect of the probiotic on menstrual symptoms, as measured by the Menstrual Symptom Questionnaire. We hypothesize that women who consume the probiotic will experience decreased menstrual symptoms compared to women who consume a placebo.To determine the effect of the probiotic on stress, as measured by daily self-reported stress and a monthly Perceived Stress Scale. We hypothesize that women who consume the probiotic will experience decreased levels of stress compared to women who consume a placebo.To determine the effect of the probiotic on stool form and frequency throughout the menstrual cycle, as measured by the Bristol Stool Form Scale. We hypothesize that women who consume the probiotic will experience a more ideal consistency and pattern of bowel habits compared to women who consume a placebo.To determine the effect of the probiotic of digestion-associated quality of life, as measured by Digestion-Associated Quality of Life Questionnaire. We hypothesize that women who consume the probiotic will experience a better quality of life compared to women who consume the placebo.To determine the effect of the probiotic on dietary intake, as measured by the Automated Self-Administered 24-hour (ASA-24). We hypothesize that energy intake will not be different between the probiotic and placebo groups.To determine the effect of the probiotic on food cravings, a measured by the Food Craving Inventory (FCI). We hypothesize that women who consume the probiotic may experience fewer cravings than women on placebo.To explore the effect of the probiotic on the gut and vaginal microbiota in a subgroup of the study population. Recovery of the probiotic in the stool and vaginal samples will be assessed. Changes in the concentrations of the probiotic will be measured with specific DNA (or antibodies) in fecal and vaginal samples (e.g., qPCR, flow cytometry, or other methods). Effects of the probiotic interventions on overall microbiota composition (e.g., Illumina 16S rRNA sequencing) will also be measured. We hypothesize that women who consume the probiotic may show changes in microbiota composition compared to women on placebo.

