#### Statistical analysis

Intent-to-treat analyses will be performed for all outcomes with all eligible participants. A compliant per protocol analysis will be conducted on the primary outcome. Participants will be considered compliant if they consume > 80% of the interventional product during the 8 weeks of the study. Since there is only a single outcome measured, no imputation will be performed for missing variables. Statistical models that account for unbalanced data will be used if warranted, to account for participate drop out. Study results will be statistically analyzed by a statistical software programs (SAS and SigmaPlot). The mean delta (difference between pre and post-supplementation) will be tested by parametric or non-parametric *t* test depending on the normality of the data. Continuous variables will be presented as means with standard errors (SEM). Categorical variables will be analyzed as count or proportions. The significance of statistical tests will be determined using a type I error rate cut-off of 0.05. Categorical variable counts and proportions will be reported along with relevant standard errors.

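### Outside the subgroup, women have one untreated dietary recall (day −7), so the recall at menstruation 2 has no untreated menstrual counterpart

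*Protocol article*

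**What the plan says.** All points are from the protocol article.

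- **Recalls for everyone (Study conduct, text after Table 1):** a "24-h dietary recall assessment at four points during the study (study days − 7, 21, 28, and 35) throughout the menstrual cycle".
- **Extra recalls (Study conduct):** "This subgroup will also complete additional 24-h dietary recalls (study days 1, 42, 49, and 56"). The subgroup's size is given there too: "A subgroup of 20 participants per arm will also be asked to sign a separate informed consent form".
- **Start of supplement:** "On the third day of their menstrual cycle (day 3/menstruation 1), they will begin consuming their study supplement (start of intervention").
- **Labels and windows:** "Study days 3, 28, and 56 will be referred to as “menstruation 1,” “menstruation 2,” and “menstruation 3,” respectively". Also, "All study days will be ± 3 days to account for variation in each participant’s menstrual cycle".
- **Outcome (Study outcomes):** dietary intake is a secondary outcome of the whole trial: "To determine the effect of the probiotic on dietary intake, as measured by the Automated Self-Administered 24-hour (ASA-24"). The stated hypothesis is that energy intake does not differ between the arms.
- **Analysis (Statistical analysis):** "The mean delta (difference between pre and post-supplementation) will be tested by parametric or non-parametric" t test. The sentence is general and is not restricted to pain.
- **For comparison:** the Food Cravings Inventory is completed by everyone on days 1 and 28, and the primary outcome is menstruation 2 minus menstruation 1.

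**The concern.** The trial's own logic is to compare the second menstruation, on supplement, with the first, before supplement. Pain and food cravings follow that logic in every woman. Dietary intake follows it only in the subgroup. For the other women, any change in intake rests on one premenstrual recall day, and the follow-up recall at menstruation has no untreated recall from the same phase.

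Two things are at stake. First, a woman's change from day −7 to day 28 or 35 contains the shift in cycle phase as well as anything the supplement does. Second, a single recall day is a noisy baseline. The hypothesis for energy intake is one of no difference, and a noisier comparison makes a non-significant result more likely, which a reader could mistake for support of that hypothesis.

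**Working it through.** **1. Which recalls are untreated.** The supplement starts on day 3.

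- Main study: untreated {−7}; on supplement {21, 28, 35}.
- Subgroup: untreated {−7, 1}; on supplement {21, 28, 35, 42, 49, 56}.

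**2. Phase matching, counted from menstruation 2 at day 28.**

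| On-supplement day | Position | First-cycle counterpart | Collected untreated? |
|---|---|---|---|
| 21 | 28 − 7 | day −7 | yes, everyone |
| 28 | menstruation | about day 1 | subgroup only |
| 35 | 28 + 7 | about day 7 | nobody; day 7 is after the day-3 start |

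The main study thus has one phase-matched pair. A day-1 recall would add a second. It would not supply a match for day 35.

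**3. How many women.** The article states no figure for diet. Its planned number reproduces: 79 / 0.85 = 92.9, so 93 per arm and 186 in total. The article does not say whether the subgroup lies inside the 93. If it does, 93 − 20 = 73 per arm (146 of 186, 78%) have no recall at menstruation 1. If it is additional, all 93 per arm lack one.

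**4. Precision.** Assume equal variance σ² for each single-day recall and one correlation r between any two recalls. The document gives no r, so a range is shown. All variances are per woman, in units of σ².

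*Unadjusted change (mean on supplement minus mean before):*

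- Planned, mean of 21, 28 and 35 minus day −7: 1 + (1+2r)/3 − 2r = (4/3)(1−r).
- Day 1 added, day 35 kept, all recalls used: (1+r)/2 + (1+2r)/3 − 2r = (5/6)(1−r). Ratio (5/6)/(4/3) = 0.625, so 37.5% lower.
- Day 1 added, only the two matched pairs (21 with −7, 28 with 1): (1+r)/2 + (1+r)/2 − 2r = 1−r. Ratio 1/(4/3) = 0.75, so 25% lower.

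These ratios hold for any r below 1.

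*Baseline-adjusted comparison (variance of the on-supplement mean, minus squared covariance over baseline variance):*

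- Planned: (1+2r)/3 − r².
- Day 1 added, day 35 kept: (1+2r)/3 − 2r²/(1+r).
- Day 35 moved to day 1: (1+r)/2 − 2r²/(1+r).

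| r | Planned | Day 1 added | Day 35 moved to day 1 |
|---|---|---|---|
| 0.1 | 0.390 | 0.382 (2% lower) | 0.532 (36% higher) |
| 0.3 | 0.443 | 0.395 (11% lower) | 0.512 (15% higher) |
| 0.5 | 0.417 | 0.333 (20% lower) | 0.417 (equal) |

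Adding day 1 gains at each r shown. Moving day 35 to day 1 loses precision under baseline adjustment when r is below 0.5.

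**The case against.** The strongest defence is that nothing in the article is misstated. One recall before treatment and three on treatment is a workable schedule for a secondary outcome, and it limits burden beside daily and weekly questionnaires. The outcome is worded as a comparison between arms, no dietary change score is defined by name, and the Abstract allows a linear model. With baseline adjustment and low r, the gain from a day-1 recall is only about 2%. All of this stands, and it keeps the point small.

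A reader might infer more than the document supports:

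- *That the dietary comparison is biased by cycle phase.* It is not. The phase shift is common to both randomised arms and cancels in the contrast between them. The subgroup's extra baseline day does not bias it either, because main study and subgroup are randomised separately.
- *That a matched pair would turn a within-arm change into a supplement effect.* Matching removes only the phase shift. Other changes over time remain, and the placebo arm is there for those.
- *That the missing day-1 recall explains day 35.* The day-3 start explains it.
- *That the whole 37.5% belongs to the matched-pair analysis.* That analysis gains 25%; the larger figure also uses the unmatched day 35.

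The defence does not remove the schedule gap. The recall days are stated in the text, and no later analysis plan can recover a recall that was not collected. Table 1 is not visible in the copy reviewed, so the reading rests on the text, which is explicit.

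**Conclusion.** The point holds as a minor, inexpensive improvement. Outside the subgroup there is one untreated recall and one phase-matched pair (−7 with 21), and the recall at menstruation 2 has no untreated menstrual counterpart. The planned comparison between arms is valid. The loss is in precision and in what can be said about within-woman change.

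The number affected (73 per arm) assumes that the subgroup is counted in the 93. The precision gains assume equal variances and a common r. They also depend on the analysis: the 25% and 37.5% figures require that the general sentence on the mean delta covers diet as an unadjusted change, which its wording permits but does not say. Under baseline adjustment the gain is about 2% to 20% for r from 0.1 to 0.5.

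**What to change.** Collect the day-1 recall in all women and keep day 35. Compare the arms on the on-supplement recalls, adjusted for the mean of days −7 and 1. Report 21 against −7 and 28 against 1 as the phase-matched changes. Because study days carry a ± 3 day window, state that the day-1 recall must be completed before the first capsule; otherwise it could fall as late as day 4 and no longer be untreated.

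Do not hold the count at four by moving day 35 to day 1. That gives up the post-menstrual recall and loses precision below r = 0.5 under baseline adjustment.

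The cost is one extra online, self-administered recall per main-study woman, which the subgroup already completes.

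The article describes the trial both as completed in December 2021 and as recruiting. If collection is over, the schedule cannot change. The remaining step is then to state that diet is compared between arms at each on-supplement recall, adjusted for day −7, and that −7 to 21 is the only phase-matched change outside the subgroup.
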